### Correlation of entomology outcomes to epidemiological endpoints

Data collected from the experimental hut trial will be used to parameterize a transmission dynamics models of malaria using previously described methods [25]. The entomological impacts of dual AI nets shall be defined by either (i) a meta-analysis of previously published experimental hut trial data, (ii) locally derived data with unwashed and washed ITNs, or (iii) locally derived data using unwashed and naturally aged field ITNs. The ability of the different models to capture the changes in malaria prevalence observed in the different study arms of the cRCT will be statistically characterized to determine whether projections based on local experimental hut trials or naturally-age field ITNs are more reliable.

### Sample size calculations

Sample size calculations are performed based on previous ITN durability data from Benin. For cohort 1, a sample size of 750 nets of each brand from 250 randomly selected households (assuming ~ 3 ITNs are distributed per household) in 5 study clusters was found sufficient to detect a 9.4% absolute difference (hazard ratio = 0.87) in ITN attrition rate assuming an attrition rate in the control arm of 70% over the 3 years and an intra-cluster correlation coefficient of 0.03. For cohort 2, a total of 522 ITNs will need to be withdrawn over three years and assuming a loss rate of 70% a total of 1800 ITNs will be marked per study arm at baseline. To reduce the impact of the durability study on the outcomes of the cRCT, cohort 2 nets will be obtained from households in the buffer areas of the selected clusters to exclude the core areas used for the cRCT sampling.

For each experimental hut trial and at each timepoint, data on the number of mosquitoes per night and the magnitude of the different random effects (huts, sleepers, nights and observational error) will be reviewed after the first round of 9 or 13 weeks and power calculations conducted by simulation using previously described methods [33]. Power analysis will determine whether the hut trial has a desired 80% power to detect superiority in mosquito killing of any new unused dual AI ITN over the new unused pyrethroid-only net, assuming a true underlying extra mortality from the dual AI net of 40%. A second round of hut trial would be performed if the desired level of power is not achieved.

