**Methods:**

Ten clusters randomly selected from each arm of the cRCT will be used for the study. A total of 750 ITNs per type will be followed in 5 study clusters per arm to assess ITN attrition and fabric integrity at 6-, 12-, 24- and 36-months post distribution, using standard WHO procedures. A second cohort of 1800 nets per type will be withdrawn every 6 months from all 10 clusters per arm and assessed for chemical content and biological activity in laboratory bioassays at each time point. Alpha-cypermethrin bioefficacy in Interceptor^®^ and Royal Guard^®^ will be monitored in WHO cone bioassays and tunnel tests using the susceptible *Anopheles gambiae* Kisumu strain. The bioefficacy of the non-pyrethroid insecticides (chlorfenapyr in Interceptor^®^ G2 and pyriproxyfen in Royal Guard^®^) will be monitored using the pyrethroid-resistant *Anopheles coluzzii* Akron strain. Chlorfenapyr activity will be assessed in tunnel tests while pyriproxyfen activity will be assessed in cone bioassays in terms of the reduction in fertility of blood-fed survivors observed by dissecting mosquito ovaries. Nets withdrawn at 12, 24 and 36 months will be tested in experimental hut trials within the cRCT study area against wild free-flying pyrethroid resistant *An. gambiae *sensu lato to investigate their superiority to Interceptor^®^ and to compare them to ITNs washed 20 times for experimental hut evaluation studies. Mechanistic models will also be used to investigate whether entomological outcomes with each dual ITN type in experimental hut trials can predict their epidemiological performance in the cRCT.

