### Study design

The study area was divided into 60 clusters that were randomly assigned to the three arms of the cRCT using restricted randomization. Study nets are identical in appearance and participating households are blinded to the type of ITN they received. Field data collectors are also blinded to the allocation of households to the study arms. Ten clusters from each study arm have been randomly selected for the durability assessment (Fig. 1). Following ITN distribution, households in these clusters will be visited to mark and prospectively follow 2 separate cohorts of ITNs per arm (Cohorts 1 and 2) every 6–12 months to monitor their physical and insecticidal durability over a period of 36 months. Cohort 1 will consist of at least 750 nets from ~ 250 randomly selected households per arm (assuming 3 ITNs are distributed per household) from 5 study clusters per study arm. These nets will be followed for ITN survivorship and fabric integrity at 6-, 12-, 24- and 36-months post ITN distribution. Cohort 2 will consist of ~ 1800 nets per study arm from ~ 600 households from all 10 randomly selected clusters (60 households per cluster) per study arm to be withdrawn (and replaced with new nets) for assessment of insecticidal activity in laboratory bioassays and experimental hut trials, content of each active ingredient and for other studies. Cohort 1 and cohort 2 nets will receive separate identification numbers and would be sampled from different households to prevent the risk of destructive sampling of nets intended for ITN survivorship studies (cohort 1). Figure 2 provides a summary of the study design and studies to be performed at each timepoint.

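### Cohort 1's detectable difference (9.4 points, labelled a hazard ratio of 0.87) does not follow from its own inputs: five clusters of 150 nets at ICC 0.03 give about 30–38% power, and 0.87 is a risk ratio

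*Protocol article*

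**What the plan says.** The whole justification for cohort 1 is one sentence under Sample size calculations. Its starting point is "a sample size of 750 nets of each brand from 250 randomly selected households (assuming ~ 3 ITNs are distributed per household) in 5 study clusters". The result it claims is that these numbers are "sufficient to detect a 9.4% absolute difference (hazard ratio = 0.87) in ITN attrition rate". Control loss is put at 70% by three years, and the only clustering input is "an intra-cluster correlation coefficient of 0.03".

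The cluster count is not a slip in that sentence. The abstract's Methods paragraph says "A total of 750 ITNs per type will be followed in 5 study clusters per arm", and Study design again takes the cohort 1 nets "from 5 study clusters per study arm".

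No power, significance level or sidedness is given for cohort 1. The 80% power in the same section belongs to the experimental hut trials.

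**The concern.** Five large clusters per arm with an intra-cluster correlation of 0.03 lose most of their information to clustering, so a detectable difference below 10 points looked too small. The paired effect measures also looked incompatible: 9.4 points below 70% is not a hazard ratio of 0.87.

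Survivorship and attrition belong to the first study objective, and the Discussion says the results should inform replacement and procurement. The section on follow-up for attrition gives a reason to expect a real difference, since householders may like polyethylene less and this could affect retention of Royal Guard. If the stated sensitivity is taken at face value, a non-significant comparison may be read as evidence of similar retention when the design could not have shown otherwise. The hazard-ratio label matters because the analysis section treats attrition as survival data, so a reader will take the term literally.

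**Working it through.** **Inputs from the protocol article (Sample size calculations; Study design)**
- 750 nets per arm in 5 clusters, so m = 750/5 = 150 nets per cluster
- ICC = 0.03
- Control attrition 70%. A ratio below 1 and a 9.4-point difference give 60.6% in the comparison arm.
- The 70% is a proportion lost. The same section sizes cohort 2 with it: 522/(1 − 0.70) = 1,740, marked up to 1,800.

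**Assumed, because not stated:** two-sided 5%; 80% power where a target is needed.

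**1. Attempt to reproduce 9.4 points (pooled-variance test of two proportions, 80% power)**

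| Nets per cluster | Design effect | Effective n per arm | Detectable difference |
|---|---|---|---|
| Clustering ignored | 1 | 750 | 6.8 points |
| 3 (household as cluster) | 1.06 | 708 | 7.0 points |
| 30 | 1.87 | 401 | 9.4 points |
| 150 (as stated) | 5.47 | 137 | 16.4 points |

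The printed figure appears at 30 nets per cluster, which would be 25 clusters per arm. This suggests a calculation for another layout, but that is an inference; the document does not say so.

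**2. Power of the stated design for 70% versus 60.6%**
- Design effect = 1 + (150 − 1) × 0.03 = 5.47
- Effective n = 750/5.47 = 137.1 per arm
- SE = √[(0.70 × 0.30 + 0.606 × 0.394)/137.1] = 0.0572
- 0.094/0.0572 = 1.64
- Normal approximation: Φ(1.64 − 1.96) = 0.376
- Noncentral t, 2 × (5 − 1) = 8 df: 0.305. A beta-binomial simulation with a cluster-level t-test gave 0.306.

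**3. Difference detectable with 80% power**
- Normal, unpooled variance: 16.2 points (16.4 pooled). Hazard ratio ln(0.462)/ln(0.30) = 0.64.
- t, 8 df: 18.5 points. Hazard ratio ln(0.485)/ln(0.30) = 0.60.
- Reaching 80% for 9.4 points would take 402 independent nets × 5.47 = 2,199 nets per arm, about 15 clusters of 150.

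**4. Sensitivity to the assumptions, 5 clusters of 150**
- One-sided 5%: 44% (t) to 50% (normal)
- Difference upward, 70% versus 79.4%: 35% (t) to 44% (normal)
- ICC 0.01 to 0.05, t basis: 57% down to 21%
- ICC needed for 80% power at 9.4 points: about 0.006 (normal) or 0.003 (t), against the stated 0.03

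**5. The effect measure**
- Ratio of proportions: 0.606/0.70 = 0.866, the printed 0.87
- Proportional-hazards ratio: ln(1 − 0.606)/ln(1 − 0.70) = ln(0.394)/ln(0.30) = 0.77
- A true hazard ratio of 0.87 implies attrition of 1 − 0.30^0.87 = 64.9%, a gap of 5.1 points. About 750 × (0.70 + 0.649) = 1,012 losses would be expected. Dividing by 5.47 leaves about 185, and power by the Schoenfeld formula is about 16%.

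**The case against.** The strongest reply is that the power figures rest on unstated settings. An article may leave power and significance level to the full protocol, so their absence is not itself a fault. With a one-sided test or an upward difference, power is somewhat higher, up to about 50%. The 30% and 18.5-point figures also assume a two-arm cluster-level comparison with 8 degrees of freedom, which the analysis section does not name; the normal-approximation figures are the more neutral ones. All this stands as a caution on precision, and is why ranges are given. It does not rescue the claim: no variant tried with 150 nets per cluster and ICC 0.03 reaches 80% power for 9.4 points.

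The ICC might instead describe nets within households. The detectable difference would then be 7.0 points, so the design would do better than claimed. But the sentence speaks of study clusters, and this reading does not give 9.4 either.

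For the label, 0.70 and 0.606 could be cumulative hazards, whose ratio would be a hazard ratio. That sits badly with an absolute difference in per cent and with cohort 2, where 70% is plainly a proportion lost. It would not restore the power.

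Finally, nothing in the article says a null result will be read as no difference. That is fair: the harm is a risk of misreading, not a stated rule.

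**Conclusion.** The concern holds, and the sentence is wrong as written. With the stated cluster count, net numbers and ICC, power for a 9.4-point difference is about 30–38% at two-sided 5%, so a true difference of that size would be missed roughly two times in three. The difference detectable with 80% power is about 16–19 points, nearly double the printed value. These figures depend on the assumed significance level and power, and on the ICC applying between nets in the same study cluster.

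The mislabelling needs no assumption about power or significance level. With 70% control attrition read as a proportion, a 9.4-point reduction and a hazard ratio of 0.87 cannot both be true under proportional hazards; 0.87 is the risk ratio. This must be corrected, because it is the only sample-size justification given for cohort 1 and it concerns the first objective.

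**What to change.** Rewrite the cohort 1 sentence under Sample size calculations:
- State the power, significance level and level of clustering to which the ICC applies.
- For 5 clusters of 150 nets per arm, ICC 0.03, two-sided 5% and 80% power, give the detectable difference from 70% attrition as about 16–19 points (hazard ratio about 0.60–0.64), naming the method behind the figure chosen.
- Call 0.87 a risk ratio, or replace it with a hazard ratio of 0.77 if 70% versus 60.6% is kept as an illustration.
- If the calculation was made for a different layout or ICC, say so and reconcile it with the 5 clusters given elsewhere.

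It would also help, as a reporting preference only, to interpret non-significant attrition comparisons by their confidence intervals. At the SE above, the 95% half-width is 1.96 × 0.0572, about 11 points, which is already wider than 9.4.

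The cost is a text correction and a less favourable stated sensitivity. Nets were distributed in 2020 and surveys are complete to 24 months; no additional nets or visits are needed.

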### Experimental hut trials to assess insecticidal durability

To further assess the entomological superiority of Interceptor^®^ G2 and Royal Guard^®^ over Interceptor^®^, experimental hut trials will be performed with field collected ITNs at 12-, 24- and 36-months post ITN distribution at the Cove experimental hut station against wild free-flying pyrethroid-resistant *An. gambiae *sensu lato (*s.l*.). The Cove experimental hut station is situated in a large rice-growing field within the study area of the cRCT. The vector population at Cove exhibits intense resistance to pyrethroids [32], but is susceptible to chlorfenapyr and pyriproxyfen [30]. To provide some comparison to pyrethroid-PBO nets, PermaNet^®^ 3.0 nets (a WHO prequalified deltamethrin plus PBO ITN by Vestergaard Sarl) that were distributed by the NMCP in the Didja district (7^°^20’N 1^°^56’E) of the Zou Department, a neighbouring community to the cRCT study area, at the same time as the cRCT will also be marked at baseline and withdrawn at each annual timepoint and assessed in the experimental hut trials alongside Interceptor^®^ G2 and Royal Guard®. Three sets of hut trials will be performed: one with 12 months old field nets, the second with 24 months old field nets and the third with 36 months old field nets. Fifty-four (54) field nets of each brand will be tested in the huts at each annual timepoint for a total of 54 nights with each field net spending only 1 night in the experimental huts. Comparison will be made with new unused nets of each type. Six replicates of unused nets of each ITN type will also be tested, and each net will be given six 4 × 4cm holes prior to the trial, following WHO procedures. The hut trials will consist of the following 9 treatments:Untreated net—6 replicatesInterceptor^®^ (new unused)—6 replicatesPermaNet^®^ 3.0 (new unused)—6 replicatesRoyal Guard^®^ Benin (new unused)—6 replicatesInterceptor^®^ G2 (new unused)—6 replicatesInterceptor^®^ field net (12/24/36-months)—54 replicatesPermaNet^®^ 3.0 field net (12/24/36-months)—54 replicatesRoyal Guard^®^ field net (12/24/36-months)—54 replicatesInterceptor^®^ G2 field net (12/24/36-months)—54 replicates

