### Statistical analysis

Data from the surveys at 6, 12, 24, and 36 months will be used to calculate attrition, functional survival and median survival time using Kaplan–Meier estimators. For functional survival, nets reported as given away, sold, or stolen will be excluded from the analysis. Negative binomial regression will be used to compare hole surface area between the different ITN types. Data on WHO cone bioassays and tunnel tests will be obtained from 30 nets of each product type sampled at each time point. A chi-squared test will be used to assess the proportion of nets of each ITN type passing the WHO criteria for alphacypermethrin, chlorfenapyr and pyriproxyfen bioefficacy based on combined cone and tunnel tests. Proportional outcomes (mortality, blood-feeding, exophily) from the experimental hut trials will be compared at each time point using mixed effects logistic regression, with huts, sleepers, net replicate and nightly observational error included as random or fixed effects [33]. Numerical outcomes (hut entry) will be compared using negative binomial regression. A separate model will be fitted for each outcome to determine whether there is (i) a significant change over time, and (ii) a significant difference between ITNs washed 20 times and 36-month-old naturally aged ITNs. Analysis will be performed on STATA or the package *lme4* of the R software.

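### The hut-trial power review omits net replicate, so it can overstate power for the six-net comparison; whether the second-round decision changes depends on inputs not given, including whether the 40% is absolute.

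*Protocol article*

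**What the plan says.** Under Sample size calculations, the protocol article plans a review after the first round of each hut trial: "the magnitude of the different random effects (huts, sleepers, nights and observational error) will be reviewed after the first round of 9 or 13 weeks". Power is then simulated by a cited method (reference 33). The target is "desired 80% power to detect superiority in mosquito killing of any new unused dual AI ITN over the new unused pyrethroid-only net". The effect size is worded as "assuming a true underlying extra mortality from the dual AI net of 40"%. The article does not say whether this 40% is absolute or relative. If the target is missed, a second round follows.

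Under Statistical analysis, mortality is compared by mixed-effects logistic regression "with huts, sleepers, net replicate and nightly observational error included as random or fixed effects", citing the same reference.

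On the nets themselves, the section on hut trials for insecticidal durability says "Six replicates of unused nets of each ITN type will also be tested", while field nets are tested "for a total of 54 nights with each field net spending only 1 night in the experimental huts". The trial against washed nets has 13 treatments over 78 nights, again with six new nets per type.

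**The concern.** The two lists of model terms differ by one item, net replicate, and that item matters most for the comparison being powered. With six new nets per type, differences between individual nets average out over six units, however many nights those nets are used. A variance review without a net term would put that variation into nightly error and treat it as averaging over 54 or 78 nights.

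The review has one purpose: to decide whether a second round is needed. If power is computed without a component that the final model carries, the review could report 80% when the planned analysis has less, and the trial would stop after one round.

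**Working it through.** **Inputs from the article.** Six new nets per type. Nights: 9 weeks × 6 = 54, and 13 weeks × 6 = 78. Nights per new net if used equally: 54/6 = 9 and 78/6 = 13. The 80% is a target for a calculation made after round one, so there is no stated power to reproduce.

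**Assumptions.** The article gives no baseline mortality, catch, variance or alpha for this calculation. I take two-sided 5%, an observation-level SD s_obs of 0.5 or 0.8 logit, a between-net SD s_net of 0.3 to 1.0 logit, and m mosquitoes per hut-night as shown.

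**Formulas.** For mortalities p1 and p2 and N nights per treatment:
- d = logit(p2) − logit(p1)
- V0 = 2·s_obs²/N + [1/(m·p1·q1) + 1/(m·p2·q2)]/N, where q = 1 − p
- Review variance, with net variance absorbed into nightly error: V0 + 2·s_net²/N
- Variance with the actual net structure: V0 + 2·s_net²/6
- Power = Φ(d/SE − 1.96). The last column of the table instead uses t with 10 df, since there are 2 × (6 − 1) net-level degrees of freedom.

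The net part is understated by 54/6 = 9-fold, or 78/6 = 13-fold in the longer trial.

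**Worked case: 40% to 56%, m = 5, s_obs = 0.5, s_net = 0.3, N = 54.**
- d = 0.2412 + 0.4055 = 0.6466
- Binomial part: (0.8333 + 0.8117)/54 = 0.0305. Nightly part: 2 × 0.25/54 = 0.0093. V0 = 0.0397.
- Review: 0.0397 + 2 × 0.09/54 = 0.0431; SE 0.2075; power Φ(3.116 − 1.96) = 0.88
- Six nets: 0.0397 + 2 × 0.09/6 = 0.0697; SE 0.2640; power Φ(2.449 − 1.96) = 0.69, or 0.60 on t

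**Other cases, N = 54.**

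| Mortality | m | s_obs | s_net | Review | Six nets, normal | Six nets, t |
|---|---|---|---|---|---|---|
| 20% to 60% | 1 | 0.5 | 0.3 | 0.98 | 0.96 | 0.92 |
| 20% to 60% | 1 | 0.5 | 0.5 | 0.97 | 0.92 | 0.86 |
| 20% to 60% | 10 | 0.8 | 0.5 | 1.00 | 1.00 | 0.995 |
| 20% to 60% | 10 | 0.8 | 1.0 | 1.00 | 0.83 | 0.75 |
| 40% to 56% | 10 | 0.8 | 0.3 | 0.88 | 0.69 | 0.60 |
| 40% to 56% | 10 | 0.8 | 0.5 | 0.84 | 0.46 | 0.39 |
| 40% to 56% | 5 | 0.8 | 0.3 | 0.77 | 0.61 | 0.52 |
| 20% to 28% | 10 | 0.8 | 0.3 | 0.52 | 0.37 | 0.31 |

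In the last two rows the review is already below 80%, so the second round is triggered and the omission does no harm to the decision.

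**Where a 40-point effect would fail.** At m = 10 and s_obs = 0.8, power on t drops below 80% at s_net = 0.93 for 20% to 60%. Across baselines of 10% to 50% the threshold runs from 0.88 to 1.16.

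**If the review reads exactly 80% for 20% to 60%.** With d = 1.792, the review variance is (1.792/2.802)² = 0.409. Adding 2·s_net²(1/6 − 1/54) gives power of 0.789, 0.775 and 0.732 at s_net = 0.2, 0.3 and 0.5. With s_obs = 0.5, this starting point needs only about 0.5 mosquitoes per hut-night.

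**The case against.** The strongest reply is that little follows in practice. Extra mortality of 40% reads naturally as percentage points. On that reading, one mosquito per hut-night still leaves power at 0.86 or more for a net SD up to 0.5 (s_obs 0.5), so the decision does not change. That stands, and it limits the size of the point. It does not settle the reading: the same section writes of an absolute difference for attrition but gives no such word here.

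The article also condenses a fuller method. The list may be shorthand, and the cited simulation method, which cannot be checked here, may carry a net term. That is possible. Still, the two lists are explicit, cite the same source and disagree.

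Four stronger readings are tempting, and the article does not support them:
- **That a declared net random effect was dropped.** The analysis text says random or fixed, so net replicate is not yet declared random.
- **That a needed second round will be missed.** This depends on catches, net variance and the meaning of 40%, none of which is stated.
- **That the final mortality comparison is biased.** The analysis model names net replicate; only the power check is affected. Field nets spend one night each, so for them net and nightly variation coincide and the 6-against-54 argument does not apply.
- **That a second round would reuse the same six nets.** The article does not say so.

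**Conclusion.** The inconsistency is real. It falls on the comparison that drives the second-round rule, and its direction is known: if the review follows its own list and new nets differ at all, computed power is too high.

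Its size is conditional. For a 40-point effect the decision would normally stand, except with very sparse catches or a very large between-net SD among new nets. For a relative effect such as 40% to 56%, a net SD of 0.3 to 0.5 costs about 19 to 38 points on the normal approximation (0.88 to 0.69; 0.84 to 0.46) and 28 to 45 points when the six-net test uses t (0.88 to 0.60; 0.84 to 0.39). That can turn a pass into a fail. All of these figures rest on the assumed mortalities, catches, SDs and alpha listed above.

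**What to change.** Under Sample size calculations, add net replicate to the components that are reviewed and simulated. Simulate the actual structure: six nets per new type, each used on about 9 or 13 nights. State whether the 40% is absolute or relative.

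Under Statistical analysis, specify net replicate as a random effect nested in treatment. Each net belongs to one treatment only, so a fixed net effect would be aliased with the treatment contrast.

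The cost is one more term in a simulation already planned, plus some wording. The downside is a slightly less favourable power figure that may trigger the second round more often. As an option rather than a correction, a second round could use fresh new nets, because extra nights on the same six leave the 2·s_net²/6 term unchanged.
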